**Fig. 1 Fig1:**
[figure not shown]
Study design describing pre- and post-testing

#### Population and power calculations

Families with children, 6–10 years old with an iso-BMI ≥ 25 will be invited to participate in the study. Follow up data from 64 participants in each group will give a statistical power of at least 80 % and a 5 % significance level for comparing effect measures of MVPA (difference 15 min, SD 30 min) between the groups. To account for the expected dropout and loss of follow-up rates of 25 %, assessing a higher dropout rate for the intervention group, we intend to include a minimum of 80 participants in both the intervention group and the control group.

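### Recruiting 80 per group leaves 60, not the required 64, after the plan's own 25% loss, so power is about 77.5% rather than at least 80%

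*Protocol article*

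**What the plan says.** All the relevant figures stand in one paragraph of the protocol article, under Population and power calculations in Step 5.

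- Evaluable number and power: "Follow up data from 64 participants in each group" are said to give "a statistical power of at least 80 % and a 5 % significance level".
- Effect and variability: "effect measures of MVPA (difference 15 min, SD 30 min) between the groups".
- Expected attrition: "expected dropout and loss of follow-up rates of 25" per cent, with the qualifier "assessing a higher dropout rate for the intervention group". No separate rates are given for the two groups.
- Recruitment target offered as the allowance for that attrition: "we intend to include a minimum of 80 participants in both the intervention group and the control group".

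No other part of the article gives a different target or a different loss rate. MVPA, the outcome used for the calculation, is listed among the primary outcome variables in Step 6.

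**The concern.** The paragraph links three numbers: 64 needed at follow-up, 25% expected to be lost, and 80 to be recruited so that the first survives the second. They cannot all hold, because 25% of 80 is 20 and only 60 remain. The figure of 80 equals 64 × 1.25. This suggests, though the article does not say so, that the evaluable number was multiplied by one plus the loss rate instead of divided by one minus it.

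This is the article's only justification of its sample size. A study that recruits its stated minimum and loses what it expects to lose would fall below its own follow-up requirement and below its stated power. The expectation of higher dropout in the intervention group points the same way, since the two groups have the same minimum.

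**Working it through.** **Inputs**, all from Population and power calculations: difference 15 min, SD 30 min, significance level 5%, power at least 80%, 64 per group with follow-up data, 25% loss, 80 per group recruited. The article does not say whether the test is two-sided. It is taken as two-sided because that reproduces 64; a one-sided test would need only about 50 per group.

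**1. Reproduce the evaluable number.** The standardised effect is 15/30 = 0.5. The normal approximation gives n = 2 × (1.960 + 0.842)² / 0.5² = 62.8, so 63 per group. The exact two-sample t-test gives 63.8, so 64. The plan's 64 is correct, and it is the minimum on the t-test: 63 per group gives 79.5% power and 64 gives 80.1%.

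**2. Check the allowance for loss.**
- Retained from the target: 80 × (1 − 0.25) = 60 per group, 4 short of 64.
- Needed to retain 64: 64 / (1 − 0.25) = 85.3, so 86 per group (172 in total instead of 160). Check: 86 × 0.75 = 64.5.
- Loss that 80 does cover: 1 − 64/80 = 20%.
- The stated figure arises as 64 × 1.25 = 80.

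**3. Power at the numbers retained from 80 per group.** Two-sided 5% t-test, noncentrality 0.5 / √(1/n₁ + 1/n₂), with n₁ + n₂ − 2 degrees of freedom. The normal approximation is shown for comparison. The article gives no group-specific rates, so every row with unequal loss is an assumption.

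| Loss, intervention / control | Retained | Power, t-test | Power, normal approx. |
|---|---|---|---|
| 20% / 20% (what 80 covers) | 64 / 64 | 80.1% | 80.7% |
| 25% / 25% | 60 / 60 | 77.5% | 78.2% |
| 30% / 20% (average 25%) | 56 / 64 | 77.3% | 78.0% |
| 35% / 15% (average 25%) | 52 / 68 | 76.8% | 77.5% |
| 25% / 20% (25% read as intervention only) | 60 / 64 | 78.8% | 79.5% |
| 25% / 15% (25% read as intervention only) | 60 / 68 | 80.0% (79.99%) | 80.6% |

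**4. Put the gap in terms of the effect.** At 60 per group, 80% power requires a standardised effect of 0.516. With SD 30 that is a difference of 0.516 × 30 = 15.5 min instead of 15. With a difference of 15 it is an SD of 15/0.516 = 29.1 instead of 30.

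**The case against.** Several points can fairly be made for the plan.

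- *The power statement itself is right.* It is attached to 64 children with follow-up data, and 64 does give just over 80%. This stands: the fault lies in the step from 64 to 80. But 80 is put forward as the number that accounts for the loss, so the reader is told that the power is secured, and at 25% loss it is not.
- *80 is a minimum.* Recruiting more could close the gap. That is true, but the plan does not commit to it, and a stated minimum is the figure that has to be sufficient.
- *25% may be meant as the higher, intervention-group rate.* The wording allows this. Power then depends on an unstated control rate: 78.8% if control loss is 20%, and practically 80% if it is 15% or less. This is the most favourable reading. The intervention group is still left at 60, below the 64 asked for in each group.
- *Unequal loss adds little.* This stands. At an average of 25%, a 30/20 split costs 0.2 points against equal loss and a 35/15 split costs 0.7. The main point does not depend on these splits.
- *The gap is smaller than the uncertainty in the inputs.* This also stands as a statement of size: half a minute in the assumed difference, or one minute in the SD, makes up for it. The error biases no estimate and leaves the type I error unchanged. It does not make the printed figures consistent.

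**Conclusion.** The concern holds. On the plan's own inputs, 80 per group does not allow for a 25% loss. It leaves 60 per group instead of 64, and 86 would be needed. Power is 77.5% on the t-test that reproduces the plan's 64 (78.2% on the normal approximation), against the stated minimum of 80%.

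The size is modest: 6 recruits and 4 evaluable children per group, and about 2.5 points of power. The result assumes a two-sided 5% test and a loss of 25% in each group. With 25% as the average, the unequal splits tried give 76.8% to 77.3%. Only if 25% is the intervention-group rate and control loss is about 15% or less does power come back to about 80%, and the intervention group then still misses its stated number.

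**What to change.** Correct the paragraph in one of these ways.

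1. **Restate the power.** Say that 80 per group with 25% loss leaves about 60 per group and about 77% power for a difference of 15 min (SD 30).
2. **Restate the loss covered.** Say that 80 per group gives 80% power provided loss is at most 20% in each group.
3. **Change the target.** If 80% power is to hold at 25% loss, recruit at least 86 per group.

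In each case, state whether 25% applies to each group, to the average, or to the intervention group. If a higher intervention-group rate is expected, give both rates and divide 64 by one minus each. For illustration, assumed losses of 30% and 20% would need 64/0.70 = 91.4, so 92, in the intervention group and 64/0.80 = 80 in the control group.

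Options 1 and 2 cost one sentence, need no extra participants, and make the stated power or the tolerated loss slightly less favourable. Option 3 costs 12 more participants in total (172 instead of 160).

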### Step6: Development of an evaluation plan

The purpose of step 6 was the development of an evaluation plan. The main objectives specified in step 2 correspond with outcome variables and measurements, of which a detailed overview is described in Table 5. The primary outcome variables, measured at inclusion, at completion of the 6 months intervention and at long term follow up, are children’s MVPA, sedentary time, screen viewing time, eating habits, sleeping patterns and HRQoL as well as parental motivation and support from health care providers. The secondary outcome variables; iso-BMI of the children and parental perception of health will also be measured during pre- and post-testing described in Fig. 1.

In order to conduct a process-evaluation, important enhancers and barriers related to the adoption and implementation were identified by representatives (*n* = 3) involved in the adoption and implementation process in the pilot study. The in depth- interviews of important stakeholders identified the importance and value of having determined and highly committed initiators and project leaders, especially in the process of establishing agreements with the municipality council and other locally based partners. Barriers in the implementation process were related to poor cooperation between the program facilitators, municipal council and the health nurses. Resistance from the participating children’s parents and a lack of program funding were also identified as important barriers of adoption and implementation of the study.

## Discussion

This paper describes the developmental process and the content of a family-based intervention for improving lifestyle habits among overweight and obese children, 6–10 years old. Several studies have shown that a theory and evidence based approach increase the likelihood of positive intervention effects [30]. Despite a complex and time-consuming process, the IM protocol has been a useful tool for planning and development of the present intervention study.

Comprehensive systematic reviews highlight the successful use of multi-component interventions in the treatment of childhood obesity, and many studies have been conducted in clinical settings [29, 34, 60]. To our knowledge, only a limited number family-based, multi-component studies have been conducted in community-based settings in Norway. Thus, it was necessary to conduct a pilot study and obtain information on opportunities and barriers in order to tailor the intervention to the local conditions in Norwegian municipalities and to adapt the intervention tools and materials to health personnel conducting the study and to the target group.

Another strength of this process is the use of bottom-up approaches by including parents, public health nurses and other health personnel at Public Health Clinics (PHCs) and Healthy Life Centers (HLCs) in the planning process increases user-perspective and the likelihood of program sustainability long term. Although the interviews involved relatively few participants, they represented a broad specter of important key stakeholders influencing the weight-management program.

The research program has SDT as the main theoretical point of departure. Even though a logic model for understanding behavioral change is linear, focusing on the presumed cause-effect identified in theory and empirical research, we acknowledge that the behavioral treatment programs and proposed outcomes are part of a complex multilevel system, calling for an ecological approach. Targeting overweight and obese children and their parents is not an ultimate solution, as other environmental factors play pivotal roles that influence the children’s health-related behaviors. Parenting style and role modelling is, however, of crucial importance for children’s lifestyle behavior during this phase of life [61].

This intervention study will provide both objectively assessed data and self-reported data on both short-term and long-term effect of a multicomponent approach targeting overweight and obese children and their families. Furthermore, this study will provide practical and accessible tools and materials that can assist health care personnel in their daily practice. This program, if proven effective, may be implemented with contextual adaption in municipal health care institutions in Norway.
